##### Secondary objectives

All clinical outcomes derived from the standardised outcome framework will be analysed at 0, 24, 48 and potentially 60 and 72 weeks post-operatively. Outcomes will take the form of count (change in number of symptom episodes), ordinal (patient’s global impression of success) and continuous (questionnaire scores) data. Mixed models appropriate to the outcome data types will be fitted to estimate the treatment effect, adjusting for baseline values, gender, and breakthrough medication use as a potential confounder.

All participants randomized to the three groups will be analysed according to their allocation: we would allow for +/- 2 weeks from the scheduled intervention date. Eventual deviations from this time buffer will be taken into account by a modified intention-to-treat analysis. Analysis will be performed using proprietary software (Stata, Stata Corp. TX, USA) with *p* < 0.05 taken to indicate statistical significance.

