### Risks and benefits of participation

The risks of trial participation are considered very low over and above standard surgical risks. The intervention proposed is already offered to patients in specialist centres throughout the UK and internationally. The only difference conferred by participation is that the intervention will be randomly allocated by time and very carefully assessed. CC is a chronic condition (especially by the time conservative treatments have failed) and thus allocation to waiting times of up to 24 weeks poses no clinical risk. Radio-physiological tests (INVEST) are required to select patients with appropriate structural pelvic-floor problems for surgery. These would be performed in routine clinical practice in all patients undergoing LVMR and will also be mandated for the trial using specified techniques and equipment. While this may lead to slight variance from normal practice, the fundamental tests and their safety remain unchanged. Such tests have been performed daily in most specialist centres for up to 30 years without any recorded complication (Barts Health experience is over 10,000 patients). A small ionising radiation dose is required for two tests (covered below). A number of questionnaires contain personal questions about bowel problems and the effect of these on QOL and psycho-behavioural functioning; however, all have been used in studies of similar patients previously. The design of the study requires data collection at time points additional to those required for the analysis of the primary and secondary endpoints. However, this streamlines the logistics and management of the study participants through the course of the study whilst ensuring blinding is maintained and eliminating observer bias. This small additional burden on participants has been carefully balanced against the obvious benefits of the design and efficiencies of sample size gained, reducing the overall number of participants required to undergo surgery.

The benefits of participation are that patients will receive a very high standard of surgery (the most experienced UK surgeons will be participating). Further, by design, the fidelity of surgical technique will be standardised and tightly scrutinised (including by preceptorship and mentorship if required); they will also receive a high standard of monitored care as a consequence of the detailed protocol.

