## Design/methods

This is a stepped-wedge, randomised trial of LVMR in adults with chronic constipation (*n* = 114), which follows the “Standard Protocol Items: Recommendations for Interventional Trials” (SPIRIT) guidelines (see Additional file 3). Participants will be randomized to three equal arms (*n* = 38) with different lengths of delay before surgery. LVMR will be performed at T0 in group I; T12 (12 weeks) in group II and at T24 (24 weeks) in group III.

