#### Secondary outcomes

All outcomes within the standardised outcome framework will be analysed to compare baseline values with values at 24 and 48 weeks post-surgery follow up. When further follow-up data are obtained (time permitting) these will also be reported at the later time points of 60 and 72 weeks. The outcomes are:Response to treatment defined as a 1-point (or greater) reduction in the PAC-QOL score [74, 75].PAC-QOL: individual domains and total score (as continuous variables).PAC-SYM score: individual domains and total score (as continuous variables).A 2-week patient diary (for 2 weeks prior to each assessment) to record bowel frequency and whether each evacuation was “spontaneous (no use of laxatives) and/or complete”; a journal will also capture concurrent medication, health contacts, time away from normal activities (including work) since the patient’s last visit.Generic QOL assessment: EuroQol Health Outcome measure (EQ-5D)-5L descriptive system and EQ-visual analogue scale (VAS) [76]. Note: the EQ-VAS has SD of approximately 30 points: a 10% difference in VAS deemed clinically significant can be detected with the large sample sizes proposed.Patient Health Questionnaire-9 (PHQ-9) [58, 59].Generalized anxiety disorder questionnaire (GAD7) [60].Global patient satisfaction/improvement score (VAS) and whether they would recommend LVMR to other patients.Potentially modifiable cognitive and behavioural psychological variables shown to predict onset and perpetuation of other functional bowel symptoms: negative perfectionism [71], avoidant and “‘all or nothing” behaviour subscales of the behavioural response to illness questionnaire (CC-BRQ) [77], and brief illness perception questionnaire (BIPQ) (CC) [78].St Marks Incontinence score (for concurrent symptoms) [79].Baseline brief sexual function questionnaire (Pelvic Organ Prolapse/Urinary Incontinence Sexual Questionnaire (PISQ-12) in women [80] and Male Sexual Health Questionnaire (MSHQ)-EjD Short Form in men [81]).

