#### Visit 2 - run-in for surgical interventions

Participants will be randomized (at visit 1) to three arms with different lengths of delay before surgery. In all arms there will be a period of 4 weeks post-eligibility to arrange the logistics of surgery (T–4w to T0) and ensure that patients have returned to their normal life routine after various assessments. Subsequently, LVMR will be performed at T0 in group I (visit 2); T12 (12 weeks) in group II (visit 3) and T24 (24 weeks) in group III (visit 4).

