#### Visit 2–8 - follow-up outcome assessments

All patients will complete the standardised outcome framework (inclusive of PAC-QOL and PAC-SYM) questionnaires at T–4, T0 and 12, 24, 36, 48, 60 and 72 weeks post run-in (see Additional file 2). This ensures that 24-week and 48-week post-surgery follow-up data on the primary and secondary outcomes are collected in all patients, whilst maintaining blinding of group allocation. Thereafter, participants will leave the study and return to “routine clinical care” as determined within their local NHS institution. During the first 24 weeks post-surgery patients will be quarantined from further intervention, excepting emergency interventions (e.g. for complications).

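### Followed as written, most secondary outcomes get a before-after analysis at post-operative weeks 0, 24 and 48 that omits waiting-period scores the trial already collects

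*Protocol article*

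**What the plan says.** Methods of analysis, Secondary objectives, fixes the times for the framework outcomes: "All clinical outcomes derived from the standardised outcome framework will be analysed at 0, 24, 48 and potentially 60 and 72 weeks post-operatively". The models there adjust for baseline value, gender and breakthrough medication; no term for time since randomisation is listed. Trial outcomes, Secondary outcomes, gives the comparison: outcomes "will be analysed to compare baseline values with values at 24 and 48 weeks post-surgery follow up".

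The follow-up section has every patient complete the "questionnaires at T–4, T0 and 12, 24, 36, 48, 60 and 72 weeks post run-in", which is eight assessments. Design/methods sets the surgery times: "LVMR will be performed at T0 in group I; T12 (12 weeks) in group II and at T24 (24 weeks) in group III".

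The primary analysis differs. PAC-QOL is modelled on T0, T12, T24, T36 and T48 in all three arms, with a random participant effect and a fixed effect of time since randomisation. PAC-SYM follows the same approach.

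**The concern.** A stepped-wedge design separates the effect of surgery from change over trial time by comparing operated and waiting patients at the same visit. The primary analysis is set up to do this. The rule for the remaining outcomes (EQ-5D, PHQ-9, GAD7, CC-BRQ, BIPQ, St Marks score, diary and others) counts weeks from each patient's own operation and compares them with baseline. Followed literally, it yields an uncontrolled change score, although the Discussion gives an untreated comparison as a purpose of the design. Adding a time term later would not fully repair this, because the chosen visits overlap little between arms. At stake is the strength and precision of the evidence on the secondary outcomes; the primary result is not affected.

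**Working it through.** **Inputs.** From Sample size: 34 evaluable per arm, SD 1.5, correlation 0.5, difference 1.0, 5% level (taken as two-sided). Visits and surgery times are as above. T0 in group I is taken as pre-operative. SDs and correlations for the secondary outcomes are not given (apart from an approximate SD for EQ-VAS), so PAC-QOL values stand in.

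**Model.** Score = time term + one effect for each time since surgery + participant effect + error. With V = σ²[(1−ρ)I + ρJ], Var(estimates) = [Σ over arms of 34·X′V⁻¹X]⁻¹. Power = Φ(1.0/SE − 1.96).

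**1. The plan's own figure.** Visits T0 to T48 with categorical time give a 24-week SE of 0.276. Power = Φ(3.62 − 1.96) = 95.2%, which reproduces the stated 95% at 34 per arm.

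**2. Calendar visits under the 0/24/48 rule.**

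| Group | Week 0 | Week 24 | Week 48 |
|---|---|---|---|
| I | T0 | T24 | T48 |
| II | T12 | T36 | T60 |
| III | T24 | T48 | T72 |

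This is 3 of 8 visits per patient. Group II shares none with another arm. Groups I and III share T24 and T48, and only T24 has operated and waiting patients together. The omitted waiting scores after run-in are T0 in group II, and T0 and T12 in group III. Using T-4 as baseline adds one visit common to all arms.

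**3. Categorical visit effects on that set.** Group II has three visit means and three visit effects of its own, so it adds nothing to the surgery effect.
- 24-week effect: group I minus group III at T24. SE = √(2σ²/34) = √(4.5/34) = 0.364, power 78%, identical with group II deleted.
- With T-4: SE = √(2σ²(1−ρ²)/34) = √(3.375/34) = 0.315, power 89%, again identical without group II.
- All eight visits: SE 0.255, power 97.5%.
- 48-week effect: SE = √(4σ²(1+ρ)/34) = √(13.5/34) = 0.630 (0.514 with T-4), against 0.405 from all eight visits.
- Adding the possible 60- and 72-week points leaves both 0/24/48 SEs unchanged.
- For correlations from 0.3 to 0.7, the 24-week SE is 28% to 77% larger than with all eight visits, or 22% to 26% larger with T-4.

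**4. No time term (the literal reading), 102 patients.** All arms contribute.
- 0/24/48: SE = √(2σ²(1−ρ)/102) = √(2.25/102) = 0.149.
- With T-4: SE = √(1.5·σ²(1−ρ)/102) = √(1.6875/102) = 0.129.
- All eight visits: 0.122.

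**5. Linear time.** 0/24/48 gives 0.332 (0.251 with T-4), against 0.235 from all eight visits. Without T-4, group II supplies about 9% of the information on the 24-week effect, or about 29% if one common post-operative effect is fitted.

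**The case against.** The list of weeks can be read as reporting points. The protocol does not say that other visits are kept out of the mixed models, and a signed-off analysis plan is promised. This has force: a list of target weeks beside a mixed model is ordinary condensed wording. But the text goes further. It names a visit set different from the primary one, describes a comparison with baseline, and lists adjustment terms without time. That is a stated rule, and following it gives a before-after analysis.

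A reader might infer that a third of the patients add nothing. The documents do not support that in general. It holds only with categorical visit effects, which no section specifies; the primary analysis section leaves a linear trend open, and the literal comparison with baseline uses all three arms.

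A reader might also take the Risks and benefits remark about "data collection at time points additional to those required for the analysis of the primary and secondary endpoints" as proof that visits are excluded. It is not: the primary endpoint is the 24-week score, yet its model uses five visits, so a visit can be additional to an endpoint and still be analysed.

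Nor are all secondary outcomes affected, since the PAC-QOL and PAC-SYM totals have the T0 to T48 model. The sample size section makes no power claim for the other outcomes, so the power figures above only illustrate relative precision. Finally, omitting the 12-week score might suggest dropout bias, but sizing that needs dropout assumptions the documents do not give, and no weight is placed on it here.

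**Conclusion.** The concern holds in a limited form. For framework outcomes other than the PAC-QOL and PAC-SYM totals, the rule as written is a before-after comparison that leaves out concurrent waiting-period scores already scheduled. If visit effects are added to that visit set, the 24-week SE is 32% larger than from T0 to T48 (0.364/0.276), or 14% larger with T-4 (0.315/0.276). Against all eight visits it is 43% or 23% larger. With a linear trend and T-4 the loss against all eight visits shrinks to about 7% (0.251/0.235). With no time term the SE is small under any visit set, but the estimate then includes any change over trial time.

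These sizes rest on PAC-QOL inputs, equal correlation between visits and a two-sided 5% test. There is also a plain inconsistency: PAC-SYM falls under both the T0 to T48 model and the rule for all framework outcomes.

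**What to change.** In Methods of analysis, Secondary objectives, replace the list of analysed weeks with wording such as: each secondary outcome will be modelled on all scheduled assessments (T-4, T0 and T12 to T72), with a categorical effect of visit (time since randomisation) and a separate term for each 12-week interval since surgery; the 24- and 48-week terms are the reported results.

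State that the 48-week effect has no concurrent untreated group, because all arms are due to have been operated on at T24 and 48 weeks after surgery is first reached at T48. It therefore relies on effects by time since surgery being common to the arms. Say which of the two statements governs PAC-SYM.

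The cost is wording only; no data or visits are added. The downsides are a somewhat larger model for count and ordinal outcomes, and wider intervals than a before-after analysis would report (24-week SE 0.255 from all eight visits with visit effects, against 0.149 from 0/24/48 without a time term).

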Post-operative management will be as per routine clinical care. This is usually an overnight hospital stay followed by urinary catheter removal, mobilisation and discharge. Post-operative laxatives use is standardised to a weaning course of Movicol/Laxido three times daily (TDS) immediately post-operative for 1 day, then reduced according to ease of bowel movements. Medication will be post-operatively recorded on a drug chart by the anaesthetists. This prevents post-operative constipation from immobility, narcotics and general anaesthesia, which if left untreated may cause painful straining on the mesh and thus protracts in the sacral promontory periosteum, potentially leading to readmission. The surgeon should aim to discharge patients 1 day post-operative. Length of stay will, however, be determined by clinical evaluation and may be longer if required. Quality control of LVMR procedures will be conducted according to expert panel review, as per the relative SOP.

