#### Concomitant medications

It is inevitable that participants will seek recourse to laxatives and other dietary supplements during the course of the programme. Experience shows that complete prohibition can lead to unreported laxative use, which might confound findings. Although we will strongly discourage *ad libitum* medication usage and specify a defined breakthrough regimen, we will record co-treatment with sufficient fidelity and integrity to enable use as covariates in analyses using a specific diary for this purpose. A concomitant medications list including a shortlist of contributory or confounding medications will be used for filtering on data entry.

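### The secondary-objective models adjust the LVMR effect for on-study breakthrough medication use, which surgery can change, so they do not estimate the total effect of surgery

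*Protocol article*

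**What the plan says.** Under Methods of analysis, Secondary objectives, the protocol article states: "Mixed models appropriate to the outcome data types will be fitted to estimate the treatment effect". The same sentence fixes the covariates: "adjusting for baseline values, gender, and breakthrough medication use as a potential confounder". It applies to all clinical outcomes from the standardised outcome framework at 24 and 48 weeks after surgery, and possibly at 60 and 72 weeks.

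The Concomitant medications section says what is measured and when: "It is inevitable that participants will seek recourse to laxatives and other dietary supplements during the course of the programme". A breakthrough regimen is to be defined, and "we will record co-treatment with sufficient fidelity and integrity to enable use as covariates in analyses using a specific diary for this purpose".

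Under Secondary outcomes, a two-week diary before each assessment records whether each evacuation was "spontaneous (no use of laxatives) and/or complete".

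The models under Primary objective are different. PAC-QOL is modelled with participant random effects and a fixed effect of time, and PAC-SYM by the same approach. Neither names a medication covariate.

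**The concern.** A covariate belongs in a treatment-effect model if it is fixed before treatment, or at least cannot be changed by it. Breakthrough use during follow-up fails that test. A patient relieved by surgery needs fewer laxatives, and a patient made worse needs more. Use after surgery is therefore a consequence of surgery and lies on a path from surgery to symptoms. Comparing patients at equal medication use answers a different question from what LVMR does to symptoms overall.

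There is a second mechanism. Unmeasured severity is likely to drive both medication use and symptom scores. Once surgery also affects use, conditioning on use links surgery with severity among patients who had the same use (collider bias), even where surgery timing was randomised.

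For the laxative-free evacuation outcome, the covariate is partly the outcome itself.

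At stake is how the secondary efficacy results can be read, including the 48-week results that carry the medium-term effectiveness objective. PAC-QOL and PAC-SYM are listed again under Secondary outcomes. The same 24-week scores could therefore be reported with two treatment effects of different meaning, and nothing would tell the reader so.

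**Working it through.** **1. Is the covariate a baseline value?** The covariate list names baseline values as a separate item and puts no baseline restriction on medication. The Concomitant medications section describes use during the programme, recorded by diary so that it can serve as a covariate. The plain reading is on-study use: pre-surgery values from waiting participants and post-surgery values from everyone operated on.

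**2. What is being contrasted?** Surgery is at T0, T12 and T24.

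| Weeks after surgery | Group I | Group II | Group III |
|---|---|---|---|
| 24 | T24 | T36 | T48 |
| 48 | T48 | T60 | T72 |

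At 24 weeks after surgery, only group I has an unoperated comparator at the same calendar time, namely group III just before its T24 operation. From 48 weeks on, all arms are scheduled to have been operated on, so the contrast is before-after. In both settings, post-surgery medication use is downstream of surgery.

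**3. The plan's own figures.** They are not in dispute and they reproduce. The check used generalised least squares with SD 1.5, correlation 0.5, assessments at 0, 12, 24, 36 and 48 weeks, categorical time, a separate effect for each time since surgery, and a two-sided 5% test of a 1.0-point effect at 24 weeks. The smallest group size reaching 95% power is 34 per arm (95.2%). Then 34/0.9 = 37.8, rounded up to 38, and 3 x 38 = 114. At 38 per arm, correlations of 0.3 and 0.1 give 94.5% and 94.6%, consistent with the stated minimum of 90%.

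**4. What the covariate does to the estimate.** Every medication figure here is an assumption, because the article gives none. Let

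- t = total effect of surgery, set to -1.0 point;
- d = change in the share using breakthrough medication caused by surgery;
- b = score difference between users and non-users at the same surgery status.

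With no unmeasured common cause of use and score, the adjusted estimate is t - b x d. For example, b = +0.5 and d = -0.3 give -1.0 - (0.5 x -0.3) = -0.85. With b = +1.0 and the same d, the result is -0.70. The loss is therefore 0.15 to 0.30 points.

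A large-sample simulation (400,000 patients, two groups, 60% use without surgery) checks this. It also adds unmeasured severity: a standard normal variable worth 0.75 points per unit on the score, with correlation 0.7 with the tendency to use medication.

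| d | b = +0.5, no severity link | b = +0.5, severity link | b = -0.5, no severity link | b = -0.5, severity link |
|---|---|---|---|---|
| -0.1 | -0.951 | -0.862 | -1.054 | -0.961 |
| -0.2 | -0.893 | -0.727 | -1.100 | -0.932 |
| -0.3 | -0.845 | -0.597 | -1.148 | -0.891 |
| -0.4 | -0.802 | -0.448 | -1.197 | -0.850 |

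Here b = +0.5 means that use marks worse symptoms, and b = -0.5 that medication relieves them. Without the covariate, the same data return -0.995 to -1.006. Set against the unadjusted estimate from the same data, the departure runs from 0.03 points (-0.995 against -0.961) to 0.55 points (-1.000 against -0.448).

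This shows the mechanism and is no forecast. It is a two-group comparison without the baseline score. The plan's models include baseline values, which would absorb some of the severity, so the severity-link columns may exaggerate the departure.

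**The case against.** Four counter-arguments deserve weight.

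- **The main efficacy analyses do not use the covariate.** This stands. The PAC-QOL and PAC-SYM models under Primary objective name no medication term, so unadjusted 24-week estimates will exist whatever the secondary models do. A reader might infer that the primary result is compromised; the article does not support that.
- **Randomisation does not dispose of confounding everywhere.** This also stands. It is tempting to argue that use cannot be a confounder because the date of surgery is randomised. That fits only the randomised part of the contrast. In the before-after comparisons at 48 weeks and later, a change in co-medication is a co-intervention that randomisation does not balance, and wanting to account for it is understandable. But post-surgery use is still affected by surgery, so adjusting for it does not recover the total effect.
- **The post-operative laxative course is weak evidence.** A reader might take "Post-operative laxatives use is standardised to a weaning course of Movicol/Laxido" as proof that surgery itself sets the covariate. The fixed part lasts one day and is then reduced according to ease of bowel movements, whereas the analyses are at 24 weeks or later with a two-week diary window. Nothing shows that the course reaches those windows, so the point does not rest on it.
- **The direction is not fixed.** A reader might infer that adjustment must remove part of the surgical benefit. The table shows an enlarged effect when medication relieves symptoms and severity does not drive use. Nor is the covariate purely post-surgical, since waiting participants contribute pre-surgery values.

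None of this makes an on-study variable that surgery can change a suitable covariate for a model said to estimate the treatment effect.

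**Conclusion.** The point holds for the secondary-objective models. As written, they condition on breakthrough medication use that includes post-surgery use, and so do not estimate the total effect of LVMR. For the laxative-free evacuation outcome, the covariate also overlaps with what is being measured.

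Understatement is likely if use tracks symptoms, and overstatement is possible if medication relieves them. The size cannot be determined from the article. Under the assumed values, the adjusted estimate lies between -0.45 and -1.20 for a true -1.0, with departures as small as 0.03 points. The 1.0-point scale is borrowed from the sample size section for orientation only.

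The conclusion assumes that the covariate is on-study use, as the Concomitant medications section indicates, and that surgery can alter it. The primary PAC-QOL model, the PAC-SYM model beside it and the sample size are unaffected.

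**What to change.** In the secondary-objective models:

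- Remove on-study breakthrough medication use from the covariates of the main analyses.
- Adjust for pre-randomisation variables only: the baseline value of the outcome, sex and, if wanted, medication use recorded at screening. Medication usage is already part of the structured history taken at Visit 1, before randomisation.
- If a model adjusted for on-study medication is kept, label it exploratory and state that it is not the treatment-effect estimate. Leave the laxative-free evacuation outcome out of it, or explain the overlap.

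The cost is a line or two in the protocol or analysis plan. No data collection, visit or sample size changes. The change should be made before the analysis plan is signed off, so that the covariate set is not chosen with results in view.
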